#### The objectives of phase 2b study

The primary objective of the study is to compare duration until weaning supplemental oxygen in the two groups of treatment before or at day 15.

The secondary objectives of the study are the comparison between two groups of:
Evolution of National Early Warning Score (NEWS 2) [20]Changes in the 7-point ordinal scale between baseline and day 15Improvement of one category from admission using the 7-point ordinal scaleNormalization of feverDuration of oxygen therapy over 29 daysOxygen requirement over 29 daysTime to weaning in supplemental oxygen and proportion without O2 requirement at D15Transfer to ICU with need for invasive mechanical ventilation or high flow O2Hospital length of stayAll cause of mortalitySafety of XAV-19

To note*,* two ancillary studies will complete the phase 2b. For the pharmacokinetic study, 16 patients will be included, as for the immuno-monitoring study 30 patients will be included. Analyses performed will be identical to those performed in the phase 2a study.

Study sites involved in these ancillary studies will propose to their first patients to participate to these studies. Patients can participate simultaneously to both studies.

The objective of the pharmacokinetic study is to characterize pharmacokinetics (PK) of XAV-19-infected patients over time from D1 to D29. Pharmacokinetic analysis corresponds to antibody titer measurements at day 1 (pre-dose, post-dose), day 3, day 5 (pre-dose, post-dose), day 8, day 15, and day 29.

Objectives will be to assess the effects of neutralizing antibodies use on virus-induced immune response on longitudinal follow-up and to identify targets for “immuno-monitoring” for the next phase of the study and to investigate the immunogenicity of COVID-19 during treatment with XAV-19.

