The primary endpoint of the phase 2b is the time to weaning of supplemental oxygen.

If patient is still on oxygen at day 15 or if the patient is weaned but put back on oxygen, then the delay will be censored at 15 days.

The secondary endpoints are the:

National Early Warning Score (NEWS2) at day 15 and difference in NEWS2 between day 1 and day 15Clinical status using the 7-point ordinal scale assessed at day 3, day 5, day 8, day 11, day 15, and day 29Time to improvement of one category from admission using the 7-point ordinal scaleTime to first fever normalization (criteria for normalization: temperature < 36.6 °C armpit, < 37.2 °C oral, < 37.8 °C rectal or tympanic)Duration of oxygen therapy over 29 daysComparison of oxygen requirement between the two groups over 29 daysTime to weaning in supplemental oxygen and proportion without O2 requirement at day 15, according to baseline (day 1) oxygen requirement (≤ 4 L/min or 4 L/min)Incidence and duration of non-invasive ventilation or high flow oxygen devices, of invasive mechanical ventilation during the studyHospital length of stayAll-cause mortality at Day 29Safety of XAV-19 evaluated as:Occurrence of all suspected XAV-19-related adverse effects or incidence of serious adverse eventsProportion of participants with treatment emergent adverse events leading to study drug discontinuationIncidence of major or opportunistic bacterial or fungal infectionsIncidence of hypersensitivity reactions and infusion reactionsWhite cell count, hemoglobin, platelets, creatinine, ALT, AST, on day 1, day 3, day 5, day 8, day 11, day 15, and day 29SARS-CoV-2 viral load over time (day 1–day 29), as collected by nasopharyngeal swab samplesTime to RT-PCR virus negativity in nasopharyngeal swab samples

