### Sample size {14}

As it is a phase 2a, the number of patients was determined according to phase 2a’s relevant publications [23–25] . It was decided to enroll two cohorts of 8 patients (6 treated patients and 2 matching placebo in each cohort).

For the phase 2b, the predetermined sample size, controlling for the α risk of 5% and power of 80%, is 352 participants, based on an expected survival rate of patients giving up oxygen therapy at least at day 15 of 80% in the control group and 90% in the experimental group. In addition, the median duration of oxygen therapy in the control group is 8 days, and in the experimental group is 6 days. Hence the estimated hazard ratio is 0.75. The sample size was calculated following the formula of Schoenfeld [26] and the hazard ratio was estimated thanks to Cortes’ publication [27].

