## Assignment of interventions: allocation

### Sequence generation {16a}

Randomization will be performed and balanced by blocks. The software used for the randomization is SAS version 9.4.

In terms of the ratio, for phase 2a, the first 2 patients in each cohort will have a ratio of 1:1, and if all goes well, the remaining 6 patients in the 2 cohorts will have a ratio of 1:5 (1 placebo for 5 doses of XAV-19). For the phase 2b, it will be carried out in a 1:1 ratio.

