## Statistical methods

### Statistical methods for primary and secondary outcomes {20a}

For the phase 2a study, the safety population included all subjects randomized into the study who received at least one dose of study drug. The intention-to-treat (exposed, ITT[E]) Population was defined as all subjects who met study criteria and were randomized into the study with documented evidence of having received at least one dose of randomized treatment and at least one post-baseline XAV-19 IgG SARS-CoV2 titer measurements. The Per-Protocol Population was defined as all subjects included in the ITTE Population excluding those who had at least one major protocol deviation.

The primary endpoint will be evaluated for ITTE Population by a Kruskal-Wallis test between all placebo patients and all treated patients.

Groups of treatment will be described according to variables in of the secondary endpoints. Categorical variables will be summarized by percent and continuous variable by means and standard error, and medians and interquartile range.

For the phase 2b, categorical variables will be summarized by percent and continuous variable by means and standard error, and medians and interquartile range. Survival rate and duration of oxygen therapy will be compared between the two groups for the primary endpoints.

For the secondary endpoint, quantitative endpoint will be compared using linear mixed model and qualitative data with logistic mixed model to take into account stratification factors. Time data’s will be analyzed using survival model. Fine and Gray method will be used to take into account competing risk.

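### The phase 2b analysis section compares two quantities for what is elsewhere one primary endpoint, and does not say which one decides the trial

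*Protocol article*

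**What the plan says.** Three places in the protocol article point to a single primary comparison in phase 2b:

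- Objectives of phase 2b: to "compare duration until weaning supplemental oxygen in the two groups of treatment before or at day 15".
- Outcomes {12}: "The primary endpoint of the phase 2b is the time to weaning of supplemental oxygen". Patients still on oxygen at day 15, or weaned and put back on oxygen, are censored at 15 days.
- Sample size {14}: "controlling for the α risk of 5% and power of 80%, is 352 participants". The inputs are one hazard ratio of 0.75, Schoenfeld's formula, rates off oxygen by day 15 of "80% in the control group and 90% in the experimental group", and median oxygen durations of 8 and 6 days.

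Statistical methods {20a} puts it differently: "Survival rate and duration of oxygen therapy will be compared between the two groups for the primary endpoints". It attaches no test, model or decision rule to that sentence. The next paragraph, which opens with the secondary endpoint, brings in mixed models, including "qualitative data with logistic mixed model to take into account stratification factors", then survival models and the Fine and Gray method.

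On allocation, Sequence generation {16a} says "Randomization will be performed and balanced by blocks" and names no stratification factor. Baseline oxygen appears in Outcomes {12} only within a secondary endpoint: time to weaning and the proportion off oxygen at day 15, "according to baseline (day 1) oxygen requirement", with 4 L/min as the cut.

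**The concern.** A confirmatory comparison needs one stated quantity and one stated test. The article's own usage suggests that the two terms in Statistical methods {20a} are different things. Sample size {14} uses survival rate for the share of patients off oxygen by day 15, and gives the median duration of oxygen therapy as a separate figure. Outcomes {12} lists a day-15 proportion (by baseline oxygen) and a 29-day duration of oxygen therapy among the secondary endpoints, so two quantities of the secondary kind reappear as primary in the analysis section.

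If the two comparisons are separate tests, the result depends on an unwritten rule. If either may count, the false-positive rate exceeds 5%. If both must succeed, power falls below what the sample size assumed. A reader of the results could not tell which rule had been intended.

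The reference to stratification factors adds a smaller inconsistency. Either such factors exist and the randomisation section leaves them out, or the analysis section refers to something that does not exist. As printed, they enter only the secondary models.

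**Working it through.** **1. The plan's own sample size.** Inputs from Sample size {14}: hazard ratio 0.75, α 5%, power 80%, 80% and 90% weaned by day 15 (mean 85%). Allocation is 1:1.

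Schoenfeld: events = 4(z_α + z_β)² / (ln HR)², with (ln 0.75)² = 0.0828.

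- One-sided 5%: 4(1.645 + 0.842)² / 0.0828 gives 299 events; 299 / 0.85 gives 352 patients.
- Two-sided 5%: 4(1.960 + 0.842)² / 0.0828 gives 380 events; 380 / 0.85 gives 448 patients.

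The stated 352 is reproduced exactly with a one-sided 5% level; the article does not state sidedness. With 352 patients (about 299 events), a two-sided 5% test has about 70% power. For this point, what matters is that the calculation serves one time-to-event test.

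**2. Type I error if either of two tests may count.** Simulated null trials: 176 per arm, follow-up censored at day 15, each test two-sided at 5%.

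| Pair of tests | Setting | Each alone | Either |
|---|---|---|---|
| Log-rank, day-15 proportion | exponential times, 80% weaned | 5.0%, 5.0% | 7.1% |
| Log-rank, day-15 proportion | 85% weaned | 5.1%, 5.1% | 7.5% |
| Rank test of duration, day-15 proportion | exponential times, 80% weaned | 5.0%, 5.0% | 8.3% |

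Each row rests on 20,000 trials. In the first row the two statistics correlate at 0.90, so the inflation is modest. Two independent tests would give 1 − 0.95² = 9.75%.

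**3. Power if both must succeed.** Control 80% weaned by day 15, weaning-rate ratio 1/0.75 = 1.33, 5,000 trials: log-rank alone 69%, day-15 proportion alone 58%, both 55%. A separate run gave about 54% for both. Type I error cannot exceed 5% under this rule.

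**4. Stratifying by day-1 oxygen.** The documents give neither the share of patients above 4 L/min nor how much more slowly they wean. Assumption: half are above the cut, with the weaning hazard ratio below. Treatment ratio 1.33, two-sided 5%, 4,000 to 8,000 trials per row.

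| Assumed prognostic HR | Unadjusted log-rank | Stratified log-rank |
|---|---|---|
| 1 | 68% | 68% |
| 0.7 | 68% | 69% |
| 0.6 | 66% | 70% |
| 0.5 | 63% | 69% to 70% |
| 0.4 | 57% | 69% |

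Under the null, the unadjusted test rejected in 5.2% to 5.7% of trials and the stratified test in 5.1% to 5.6% (Monte Carlo standard error about 0.35 points). The covariate makes no material difference to type I error.

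**The case against.** The strongest reply is that the sentence loosely describes one survival analysis. Sample size {14} uses the same two terms as inputs to a single calculation with one α and one hazard ratio, and the objective and the outcome definition agree on one endpoint. No section says that each quantity is tested at 5%, or that either result would count as success. This stands as far as it goes: a reader might infer that the plan inflates type I error, and the article does not support that as a fact. It does not remove the conflict between a single endpoint in Outcomes {12} and two compared quantities under a plural in Statistical methods {20a}.

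A reader might also infer that the primary analysis ignores baseline oxygen, and that this inflates type I error or forfeits a known amount of power. The article does not support this either. It names no covariates for the primary analysis and does not exclude them; that choice is commonly left to the analysis plan, which is not shown. An unadjusted log-rank test is valid, and the gain from stratifying rests wholly on assumed figures. Stratification is therefore a recommendation here and not a defect.

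The names of any stratification factors may likewise stand in the full protocol. That explains why they might be absent from the randomisation section, but the two sections as printed still need to agree.

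**Conclusion.** The point holds as an inconsistency in the definition of the primary analysis. The objective, the outcome definition and the sample size describe one time-to-weaning endpoint and one test. The analysis section names two quantities and gives no rule for which decides.

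The consequence is conditional. With two separate two-sided 5% tests, an either-one rule gives a type I error of about 7% to 8%, under 176 per arm and 80% to 85% weaned by day 15. A both-must-succeed rule keeps type I error at or below 5% but lowers power at a hazard ratio of 0.75 from about 69% to about 54%. If the sentence means one survival comparison, neither cost arises and only the wording is at fault.

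Stratifying by day-1 oxygen leaves type I error unaffected. Its power gain is about 0 to 2 points at a prognostic hazard ratio of 0.7 to 1, about 6 at 0.5 and about 12 at 0.4, all with an assumed 50:50 split. The mismatch over stratification factors is a minor, separate inconsistency.

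**What to change.** In Statistical methods {20a}, name one primary test for phase 2b: a log-rank test of time to weaning by day 15, with the hazard ratio from a Cox model as the single named estimate. State the sidedness of the 5% level. Label the day-15 proportion off oxygen and the median duration of oxygen therapy as supportive, without a claim of success attached.

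Preferably, stratify that test and the Cox model by day-1 oxygen requirement (up to 4 versus above 4 L/min) and by any factor used in randomisation. Make Sequence generation {16a} and Statistical methods {20a} name the same factors, or remove the reference if there are none.

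The cost is wording in the protocol and the analysis plan. The covariate is already collected, no patient or visit is added, and no interim analysis is planned, so the change can be made before the blind is broken.

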### Adverse event reporting and harms {22}

All patients will be closely monitored during both study phases for overall biological and clinical safety data (e.g., infections or malignancies) and any drugs toxicity.

According to regulation, each AE reported by the patient or identified by the investigator must be collected and reported to sponsor, as soon as he is aware, if it meets to seriousness criteria from inclusion of the subject, to the end of the participation.

As a routine precaution, patients enrolled in this trial must be observed for at least 2 h post infusion of study drugs. Patients will be assessed for signs or symptoms of any infusion reactions (e.g., hypotension, hypoxia, tachycardia, fever, nausea, fatigue, headache, myalgia, and malaise).

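### Phase 2b safety incidences fall under a logistic mixed model that gives no finite odds ratio if an arm has no events; sparse safety endpoints need an exact or penalised method

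*Protocol article*

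**What the plan says.** Three places in the protocol article have to be read together.

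- *The objectives of phase 2b study* opens its list with "The secondary objectives of the study are the comparison between two groups of" and ends that list with the safety of XAV-19.
- *Outcomes {12}* names the safety endpoints of phase 2b as secondary endpoints. They include suspected drug-related effects and serious events, discontinuation because of adverse events, major or opportunistic infections, and hypersensitivity together with infusion reactions.
- *Statistical methods for primary and secondary outcomes {20a}* then says how secondary endpoints are compared: quantitative ones by a linear mixed model, and "qualitative data with logistic mixed model to take into account stratification factors". It makes no exception for safety or for rare events, and it names no test statistic (Wald, score or likelihood ratio).

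The same section also says "For the phase 2b, categorical variables will be summarized by percent". That sentence concerns description and stands beside the comparison rather than replacing it. For phase 2a the section says only that groups will be described on the secondary endpoints; for phase 2b it says compared.

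**The concern.** A logistic model estimates a log odds ratio. If one arm has no events, the likelihood keeps rising as that parameter goes to infinity, so there is no finite maximum-likelihood estimate. Software stops at an arbitrary large value with an enormous standard error. This could happen for any safety incidence that is rare on placebo.

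The safety comparison carries weight here. The article says that XAV-19 itself had not been given to humans, and only 12 patients receive it in phase 2a (two cohorts with 6 treated each). Phase 2b therefore supplies most of the controlled safety evidence. If the stated method breaks down for a rare endpoint, the comparison has no usable effect estimate, and its p-value depends on a choice that the text leaves open.

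**Working it through.** **Arm size.** The plan gives 352 patients ("controlling for the α risk of 5% and power of 80%, is 352 participants") and, for allocation, "For the phase 2b, it will be carried out in a 1:1 ratio", so 352 / 2 = 176 per arm. The 352 can be reproduced with Schoenfeld's formula, from the stated hazard ratio of 0.75 and weaning proportions of "80% in the control group and 90% in the experimental group" (mean 85%). Events = 4 × (1.645 + 0.842)² / (ln 0.75)² = 24.73 / 0.0828 = 299, and 299 / 0.85 = 352. This uses a one-sided 5% level, which is a separate matter. Only the 176 is used below. The plan gives no safety rate or safety power to reproduce.

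**Step 1: an empty placebo arm.** Tables of k/176 on XAV-19 against 0/176 on placebo, without strata, two-sided p-values:

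| k v 0 | Wald | Likelihood ratio | Fisher |
|---|---|---|---|
| 3 | 0.999 | 0.041 | 0.248 |
| 5 | 0.999 | 0.008 | 0.061 |
| 6 | 0.999 | 0.004 | 0.030 |
| 8 | 0.999 | 0.0008 | 0.007 |

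The fitted log odds ratio stops near 22 with a standard error of about 16,000. The Wald p-value therefore does not respond to k. The likelihood-ratio statistic stays finite: 2 × [log-likelihood at k/176 and 0/176 minus log-likelihood at the pooled rate k/352]. A random intercept for 35 centres, tried with ten random placements of the events for each of k = 5, 6, 8 and 10, gave likelihood-ratio p-values below 0.05 every time (median 0.008 at 5 v 0).

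**Step 2: is the likelihood-ratio test a full rescue?** Summing the binomial probabilities of all tables with p < 0.05, at the same true rate in both arms, gives its actual type I error: 9.4% at a 1% rate and 9.1% at 1.5%, against a nominal 5%. Fisher's test at 1% has 0.3%, so it errs in the opposite direction. The likelihood-ratio test also still supplies no finite odds ratio.

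**Step 3: how often is the placebo arm empty?** P(0 of 176) = (1 − p)^176, with p assumed: 84% at 0.1%, 41% at 0.5%, 17% at 1%, 3% at 2% and 0.5% at 3%.

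**Step 4: consequence for power.** Exact enumeration, 176 per arm, two-sided 5%, assumed 5% rate on XAV-19; tables with an empty arm count as non-significant for Wald, as step 1 justifies:

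| Assumed placebo rate | Fisher | Wald |
|---|---|---|
| 0% | 88% | 0% |
| 0.5% | 67.5% | 32% |
| 1% | 49% | 35% |
| 2% | 23% | 23% |

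The loss under Wald is total at 0%, about 36 percentage points at 0.5%, about 13 at 1%, and absent at 2%.

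**The case against.** A reader might infer that a real excess of hypersensitivity to the swine antibody would be reported as non-significant. The article does not support that. It specifies a model and not a Wald test, and the likelihood-ratio test from the same model gives p = 0.008 at 5 v 0, where Fisher's test gives 0.061. This part of the objection stands. It does not clear the method, because the likelihood-ratio test is too liberal with sparse data and leaves the odds ratio undefined.

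A second tempting inference is that the placebo count will be zero. The article gives no rates. Hypersensitivity is listed together with infusion reactions, and the harms section has staff look for "signs or symptoms of any infusion reactions (e.g., hypotension, hypoxia, tachycardia, fever, nausea, fatigue, headache, myalgia, and malaise". Many of these are plausible in inpatients with COVID-19 in either arm, so the combined endpoint may not be sparse at all. Whether discontinuations or opportunistic infections are rare is equally an assumption.

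A third is that the trial could not answer its safety question. Percentages by arm are planned, and the Data and Safety Monitoring Committee reviews accumulating data, so an imbalance such as 8 v 0 (8/176 = 4.5 percentage points) would be visible. What suffers is the formal comparison.

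Nor can one say that the random effect must fail across 35 centres: the text speaks of stratification factors and does not name centre as the random effect.

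Finally, a fallback for sparse events is often placed in the statistical analysis plan, which is not at hand. That lowers the weight of the point. It does not remove it, because the article states one method for all qualitative secondary data with no exception.

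**Conclusion.** The point holds in a limited form. Read together, the objectives, outcomes and methods sections place the phase 2b safety incidences under a logistic mixed model. With an empty arm that model gives no finite odds ratio or Wald interval, and its p-value is either uninformative (Wald) or too liberal (likelihood ratio, about 9% at an assumed 1% rate in both arms).

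The size depends on the placebo rate, which is assumed throughout: large at 0% to 0.5%, moderate at 1%, nil at 2%. The power figures also assume 5% on XAV-19, 176 evaluable patients per arm, and no strata. This is a minor matter, worth changing because the better method costs almost nothing.

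**What to change.** In the statistical methods section (or in the analysis plan, if it is still open), keep the logistic mixed model for common binary endpoints. Add one sentence: for the safety incidences, and for any binary endpoint with few events (for example fewer than about 10) or an empty cell, report the risk difference with an exact or Miettinen-Nurminen 95% confidence interval and Fisher's exact test. If the stratification factors are to be kept, use Firth-penalised or exact stratified logistic regression instead. Applying the rule to all listed safety incidences from the outset avoids choosing the method after seeing the counts.

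No extra data or patients are needed. The small cost is that the unadjusted exact test ignores the stratification factors and is conservative.

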### Interim analyses {21b}

No interim analysis will be performed and no early stopping rule for futility will be proposed.

### Methods for additional analyses (e.g., subgroup analyses) {20b}

The PK Concentration Population included all subjects who received XAV-19 at least once during the study. The PK Summary Population included subjects with an evaluable pharmacokinetic profile of XAV-19 on day 8. The PK/PD Summary Population included subjects who met the criteria for both PP Population and PK Summary Population.

The pharmacokinetic analysis will be evaluated by the study of the accumulation, time-invariance, achievement of steady state, and dose-proportionality by ANOVA models with terms for subjects as a random effect and day as fixed effect.

